### Recruitment

Patients will be recruited in two different ways. First, patients will be recruited from the academic outpatient treatment center at the Department of Psychology, Unit for Clinical Psychology and Psychotherapy at the Albert-Ludwigs University of Freiburg. Patients with various mental health problems and with a large variety of socio-demographic backgrounds seek treatment at the clinic. Patients can receive up to 80 sessions individual CBT at the clinic in accordance with the German national health insurance regulations. Treatment seeking individuals with severe mental disorders (e.g. schizophrenia) or acute suicidality are referred to other specialized services outside the clinic or in-patient treatment if indicated. During the intake patients will be checked on in- and exclusion criteria and receive the patient information letter if they are potentially eligible for study participation. After one week, patients will be called to check whether they are interested in participating in the study. The remaining in- and exclusion criteria will be checked, and the Structural Clinical Interview for DSM-5 Clinical Version (SCID-5-CV) interview will be conducted by phone. The procedures will take place while the patient is on a waiting list for regular treatment at the outpatient clinic. Second, individuals can sign up for the study independently of treatment in the academic outpatient treatment center. Information about the study will be put online and distributed in local health care centers. If interested, individuals will be send the patient information letter, called after one week to check remaining in- and exclusion criteria and a SCID-5-CV will be planned.

### Randomization and Procedure

Patient who are eligible to participate in the study will complete a baseline measurement and an introduction session on different days. The baseline measurement will take place in the lab and includes a measurement of learning capacity. Informed consent will be signed before the baseline measurement. The order of the measurements during the baseline measurement will be randomized for each participant in order to control for potential fatigue effects. The introduction session is conducted by the therapist and focuses on introducing the principles of CBT and completing the Core Belief Interview (CBI; McBride et al., 2007). After the introduction session, patients will be randomized into one of the three conditions ﻿using a computer script performing block randomization (1:1:1, block size = 15). Block randomization will be done by a researcher who is not involved in the study measurements. Randomization will be pre-stratified on severity of depression (mild [Beck Depression Inventory-II (BDI-II) = 14-19] vs. moderate to severe [BDI-II ≥ 20]). Therapy sessions will be completed weekly and the total study procedure from baseline measurement to the post measurement will take a maximum of 5 weeks. The researchers who perform the study measurements are blind for the therapeutic procedures. The full study procedure is also presented in Figure 2. Participants do not receive financial incentives for participation in this study.

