### Sample Size

Based on a medium effect size, alpha = .05, power =.80, number of experimental conditions = 3, number of repeated measurements = 2 to 4 (G*power (Faul et al., 2007)), a total sample size of 102 to 120 participants would be needed to detect a main effect, and 42 to 57 participants to detect an interaction in a repeated measures ANOVA. Simulation studies suggest 80 to 100 participants to detect an interaction effect between three groups (Shieh, 2019) while simulation studies on multilevel analyses suggest *n* = 80 participants to detect a medium effect size with power =.80 (Aarts et al., 2014). Taking into account 20% drop-out, we aim to include a total of 150 participants.

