##### Memory Functioning: Visual Working Memory

Visual working memory will be measured using the probe change detection task (PCDT; Dai et al., 2019). The PCDT consists of the following steps: 1. Participants are instructed by an arrow on their screen to focus on the left or right side of the screen (200 ms), 2. After a short break (300 ms) the screen is filled with colored squares on a gray background (100 ms). The squares are equally distributed between the left and right side of the screen. Participants are instructed to remember only the squares on the side that was instructed under Step 1, 3. After a second blank screen (900 ms), participants see again a field with colored squares (750 ms) and have to indicate whether the squares on the side of the screen are the same as under Step 2. Set sizes of the trial different between 8 to 12 colored squares in total. Participants will receive a total of 300 trials. Reliability and validity has been supported (i.e., test retest reliability between .52-.75; Dai et al., 2019).

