### Data Analyses

All statistical tests will be two-tailed (significance level alpha .05). Descriptives (means, standard deviations) for all measures will be provided for each condition. All analyses will be intention-to-treat and missing data will not be imputed.

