#### Main Analyses

The main analyses will be conducted in Stata. First, to test the direct effects of the different procedures on change in therapy processes and symptoms, differences on the primary and secondary outcomes between conditions (CBTSAP versus active control; CBTSAP versus CBTSAP + mental imagery; active control versus CBTSAP + mental imagery) will be tested using multilevel analysis with maximum likelihood estimation (measurements [Level 1] nested within patients [Level 2] nested within therapists [Level 3]). Because the WOR is only measured at two time points, differences between conditions on the WOR will be tested using a repeated measures ANOVA.

Second, to test whether the effect of the procedures is moderated by individual differences in learning capacity, learning capacity will be added as a moderator in the model. Moderation will be tested by adding learning capacity as a main factor and the interaction between learning capacity and condition to the multilevel regression model. For the WOR, the interaction will be added to the repeated measures ANOVA. Moderation of learning capacity will be tested separately for memory functioning and emotional bias. Memory functioning will be tested separately for each component of memory functioning (i.e., verbal working memory, visual working memory, long-term memory), while controlling for type I error (*p* < .016).

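### Per-patient random order of the baseline tasks balances position but leaves fatigue in each patient's score, where it slightly attenuates the learning-capacity moderation test unless position is adjusted for

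*Protocol article*

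**What the plan says.** Under Randomization and Procedure, the protocol article gives both the design choice and its purpose: "The order of the measurements during the baseline measurement will be randomized for each participant in order to control for potential fatigue effects". Allocation to condition follows later, after the introduction session.

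Under Main Analyses, the task scores serve as between-patient moderators: "Moderation will be tested by adding learning capacity as a main factor and the interaction between learning capacity and condition to the multilevel regression model". The components are not pooled: "Memory functioning will be tested separately for each component of memory functioning", with a threshold of p < .016 for each. The section mentions no term for the position at which a task was done.

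At least one task is long. For visual working memory, "Participants will receive a total of 300 trials", and the article cites a test-retest reliability of .52 to .75 for it. No section gives the length of the battery, the number of positions randomised or an expected size of fatigue.

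**The concern.** Random order is the standard device when mean performance is compared between tasks, because it breaks the link between a task and its place in the sequence. The planned moderation analysis asks something else: how patients differ from one another on the same task. If performance falls during the session, two equally able patients get different scores when one does the task first and the other does it last. The model as described would read that gap as a difference in learning capacity.

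Noise of this kind in a moderator shrinks its interaction with condition. Moderation by learning capacity is one of the trial's two main aims, and each memory component already faces the stricter threshold, so avoidable noise is unwelcome there.

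**Working it through.** **1. The plan's own figures.** Inputs from Sample Size: "Based on a medium effect size, alpha = .05, power =.80, number of experimental conditions = 3, number of repeated measurements = 2 to 4". Assumed: medium effect f = 0.25 and correlation 0.5 between repeated measures.
- Main effect: noncentrality = f² × N × m / (1 + (m − 1) × 0.5). With m = 2 and N = 120 this is 0.0625 × 120 × 2 / 1.5 = 10.0. The smallest N for 80% power is 120, 108 and 102 for 2, 3 and 4 measurements, which matches the stated 102 to 120.
- Group by time interaction: N = 42 with 2 measurements (power 0.803), and N = 57 with 3 measurements at the lower-bound sphericity correction of 0.5 (power 0.820). These match the stated 42 to 57.
- Drop-out: "Taking into account 20% drop-out, we aim to include a total of 150 participants"; 120 / (1 − 0.20) = 150.

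The plan's figures reproduce. None of them concerns task order.

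**2. Size of the order noise.** Let D be an assumed linear decline from first to last position, in SD of the task score and equal in all patients. Let K be the number of equally likely positions.
- Variance of position on a 0 to 1 scale: v = (K² − 1) / [12 × (K − 1)²]. For K = 4, v = 15 / 108 = 0.139. For K = 5, v = 24 / 192 = 0.125.
- Share of the moderator's explained variance that is kept: R = 1 / (1 + D² × v).

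**3. Effect on power.** Assumed: moderation effect f² = 0.0625, three arms, 2 numerator and N − 6 denominator degrees of freedom, noncentrality f² × R × N, alpha .016. This is a single-outcome regression, simpler than the planned multilevel model. With K = 4:

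| D (SD) | R | Power, N = 120 | Power, N = 150 |
|---|---|---|---|
| 0 | 1.000 | 49.9% | 62.4% |
| 0.2 | 0.994 | 49.6% | 62.1% |
| 0.3 | 0.988 | 49.3% | 61.7% |
| 0.5 | 0.966 | 48.1% | 60.5% |
| 0.8 | 0.918 | 45.6% | 57.7% |
| 1.0 | 0.878 | 43.4% | 55.2% |

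With K = 5, R is 0.970 at 0.5 SD and 0.889 at 1 SD. If all of the roughly 12 baseline instruments in Table 1 were shuffled together, v would be 143 / (12 × 121) = 0.098 and R at 1 SD would be 1 / 1.098 = 0.91. The unstandardised interaction slope shrinks by R and the standardised slope by √R (for K = 4, √0.966 = 0.983 and √0.878 = 0.937).

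**4. Fatigue that differs between patients.** Simulation with K = 4, score reliability 0.9, mean decline 0.5 SD and between-patient SD of decline 0.5. Squared correlation of the score with true ability:
- task always first: 0.900
- task always last: 0.734
- random order, unadjusted: 0.804
- random order, adjusted for position: 0.827

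**5. Why a position main effect alone is not enough.** Write the observed score as M = T − D × p, where T is true ability and p is position. A true interaction β × T × c (c = condition) equals β × M × c + β × D × p × c. The second term is position by condition. A model with position only as a main effect leaves that term out, so the M by condition slope stays attenuated. Replacing M by its residual from a regression on p, or adding both p and p × c, removes the problem when fatigue is equal in all patients.

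**The case against.** The strongest reply is that random order is conventional and has real merits. It stops any one memory component from being tied to the tired end of the session. That matters when three components are tested side by side and readers ask which of them moderates. This stands.

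A reader might infer that randomising the order fails to control fatigue altogether, or that it threatens the trial's comparisons. The documents do not support that. Allocation follows the baseline measurement, so task order cannot depend on condition. The noise can weaken a true interaction but does not create a false one.

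A reader might also infer that one fixed order would be better. That holds without reservation only if all patients tire equally. When they do not, a fixed order burdens whichever task comes last (0.734 against 0.804 under random order). Averaged over positions it can beat unadjusted random order: 0.826 against 0.795 in a variant that expresses fatigue in observed-score SD. But the cost then falls unevenly on the components. The choice is a trade-off, not a correction.

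Finally, an article may leave covariates to an analysis plan that is not shown, so the missing position term is not in itself an error. What remains is that the article presents random order as the control for fatigue, while the analysis it describes needs a further step. That step depends on position having been recorded at testing.

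**Conclusion.** The point holds as a minor loss of efficiency. Random order balances position across tasks. It does not take fatigue out of the individual score, and the moderation analysis as described uses that score without regard to position.

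The size rests on assumptions about the amount and shape of fatigue and the number of positions, none of which the documents give. For declines of 0.2 to 0.5 SD the cost is 2 points of power or less. It reaches about 7 points only at a full 1 SD with four positions. Practice or warm-up effects could offset fatigue. Under the same assumed effect, power at p < .016 is already only about 50% with 120 completers before any order noise, so task order is a small contributor. Nothing here invalidates the moderation analysis.

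**What to change.** Keep the random order. Record the position of each task for each patient at the time of testing. In the moderation models under Main Analyses, use the position-adjusted score (the residual from a regression of that task's score on its position) as the moderator. Alternatively, enter the raw score with both position and position by condition. Do not rely on a position main effect alone.

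Reword Randomization and Procedure to say that random order balances position across tasks and that the moderation analysis adjusts for position.

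The cost is one recorded variable per task and one or a few degrees of freedom per model. Adjustment removes the whole loss if fatigue is equal across patients and part of it if fatigue differs (0.827 against 0.804 in the example). A fixed order is not recommended as the default.

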### Therapists

The therapeutic procedures will be conducted by 5 licensed therapists who are working at the outpatient treatment center of the University of Freiburg. All therapist involved in this study had completed a 3-year fulltime psychotherapist CBT training course required and strictly regulated in Germany to obtain a license as clinical psychological psychotherapist. Therapist have between 5 and 29 years therapy experience. Before start of the study, the therapists received 8 hour training consisting of advanced training in CBT skills by [name] (Ohio State University), advanced mental imagery training conducted by [name] (University of Freiburg) and elaborate training on the different protocols for each therapeutic procedure in the study. All therapists will be involved in the delivery of all different procedures.

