### Therapeutic Procedures

All therapeutic procedures use techniques from the protocol for cognitive behavioral therapy (CBT; Beck et al., 1979) for depression and use agenda setting to structure the sessions. In addition, each procedure will focus on targeting the idiosyncratic beliefs and behaviors that were established during the CBI. However, the procedures differ in the number of active ingredients (see Figure 3 and data supplement 1). During the active control procedure, the therapist and patient will focus on discussion of dysfunctional thoughts and behaviors only. Therapists in this condition will be explicitly instructed to focus purely on exploring the relation between dysfunctional thinking and behavior and depressive symptoms, and not to engage in evaluating dysfunctional thinking or behavioral activation. During the CBT skill acquisition procedure (CBTSAP), the therapist and patient will choose one of the cognitive or behavioral skills from a predefined list of CBT skills (i.e., consisting of behavioral activation (behavioral therapy skill) and questions used for evaluating dysfunctional thoughts (cognitive therapy skill). Subsequently, the therapist and patient will discuss how this skill could be or have been applied in past or future situations in which idiosyncratic beliefs and behaviors may (have) lead to negative mood. During the CBTSAP plus mental imagery, the therapist and patient will not only discuss application of the skill but in addition, engage in a mental imagery exercise of skill application. The mental imagery exercise is based on a guided mental imagery procedure and has been shown to increase motivation for goal directed behaviors (Heise et al., 2022; Renner et al., 2019). During the mental imagery procedure, participants are instructed to imagine as vividly as possible and focusing on the positive aspects of the image. The procedure consists of the following steps: 1) imagine the contextual cues (e.g., place, date) of a future or past situation with depressive symptom(s), 2) engaging in multi-sensory imagery of applying the CBT skill in this situation, 3) imaging and experiencing the positive aspects related to successfully applying the CBT skill. All sessions will be videotaped for treatment fidelity checks. Research intervision will take place regularly. The agenda for each therapeutic procedure and the list of CBT skills that can be chosen from and practiced in the CBTSAP procedures is given in data supplement 1 and 2.

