
##### Idiosyncratic Thoughts and Behaviors

Idiosyncratic thoughts and behaviors will be measured with the Core Belief Interview (CBI; McBride et al., 2007). This interview will be completed by the therapist during the introduction session. Together the therapist and patient will form an idiosyncratic top three of dysfunctional thoughts and top three of dysfunctional behaviors. Note that the behaviors can both exist of the presence of unhelpful behaviors or the absence of rewarding behaviors. Based on the identified beliefs and behaviors, six idiosyncratic visual analogue scales (VAS) (0-100) will be constructed for each patient (i.e., three dysfunctional beliefs, three dysfunctional behaviors). For the dysfunctional beliefs, credibility of the beliefs and strength of related emotions will be rated. Presence, reward and pleasure related to the behaviors will be measured. The CBI has been used successfully before to establish idiosyncratic dysfunctional thoughts (Bruijniks, Los, & Huibers, 2020; Renner et al., 2018). The exact items of the CBI are given in data supplement 3.

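### One fixed, published block size of 15 leaves a small, avoidable risk that therapists who pool allocations could predict end-of-block assignments before the Core Belief Interview is set

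*Protocol article*

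**What the plan says.** The Randomization and Procedure section gives one block size: a "computer script performing block randomization (1:1:1, block size = 15"). It also names the two strata: "Randomization will be pre-stratified on severity of depression (mild [Beck Depression Inventory-II (BDI-II) = 14-19] vs. moderate to severe [BDI-II ≥ 20"]). On timing it says: "After the introduction session, patients will be randomized into one of the three conditions". On who allocates: "Block randomization will be done by a researcher who is not involved in the study measurements". Only the researchers who take the measurements are described as blind.

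The therapist acts before allocation: "The introduction session is conducted by the therapist and focuses on introducing the principles of CBT and completing the Core Belief Interview". The section on idiosyncratic thoughts and behaviours repeats this: "This interview will be completed by the therapist during the introduction session". Therapist and patient together choose three beliefs and three behaviours, and six individual 0–100 scales are built from them. Table 1 lists the Core Belief Interview under primary outcomes, and its first measurement is at the introduction session. The same beliefs and behaviours are worked on in the later sessions.

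There are five therapists, and "All therapists will be involved in the delivery of all different procedures". The Therapeutic Procedures section adds: "Research intervision will take place regularly".

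**The concern.** Within a constant block, anyone who knows the block size, the stratum, where the block started and the earlier allocations can work out what remains. Having an uninvolved researcher run the script hides the list but does not prevent this counting.

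The point matters here because an unblinded person helps to construct a primary outcome just before allocation. A therapist who expected a particular arm could, even without intending it, steer which beliefs and behaviours are chosen, how they are first rated, or how CBT is introduced. That could make the arms differ on the Core Belief Interview before treatment starts. Blind assessors could not detect or undo it, because the scales themselves would already have been shaped. The other primary instruments in Table 1 (WOR, BADS-SF, CCSC, CCL, RPI, TEPS) have an earlier lab baseline, so the exposure is mainly to this interview.

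**Working it through.** **Inputs from the article.** Block size 15 at 1:1:1, so 5 per arm per block; two strata; 150 patients; five therapists. The article gives no figure for predictability. Its own total is consistent: 120/(1 − 0.20) = 150, and 150/15 = 10 blocks if every block fills.

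**Assumptions (not in the article).** Fully informed observer: knows the block size, the patient's stratum, the block boundary and every earlier allocation in that stratum. Single therapist: knows the block size and boundary but sees only their own patients, who are spread at random over five therapists (about 3 per block).

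**Certain assignments, fully informed observer.** An assignment is certain when it and all later ones in the block belong to the same arm.

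- 15th: always, 1
- 14th: 4/14 = 0.286
- 13th: (4 × 3)/(14 × 13) = 12/182 = 0.066
- 12th: (4 × 3 × 2)/(14 × 13 × 12) = 24/2184 = 0.011
- 11th: (4 × 3 × 2 × 1)/(14 × 13 × 12 × 11) = 24/24024 = 0.001

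The sum is 1.364 per block. This agrees with the closed form b/(b − b/3 + 1) = 15/(15 − 5 + 1) = 15/11. As a share, 1.364/15 = 9.1%. Over ten full blocks, 10 × 15/11 = 13.6, or about 14 of 150. This is a ceiling, because two strata need not fill all ten blocks.

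**Best-guess rate, fixed block of 15.** The guess at each step is the arm with most places left, and its success probability is (largest remaining count)/(total remaining). Simulation gives:

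| What the guesser sees | Mean correct guess | Certain |
|---|---|---|
| All earlier allocations | 50% | 9.1% |
| Half of them | 40% | not tabulated |
| Own patients only (one fifth) | 36% | none |
| Chance | 33% | none |

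With 80% of allocations seen, certain assignments are already below 1%. Certainty therefore needs practically complete pooling.

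**Other block schemes, fully informed observer.** For the random schemes the observer knows the set of sizes but not the draws (75 patients per stratum assumed).

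| Scheme | Certain | Mean correct guess |
|---|---|---|
| Fixed 15 | 9.1% | 50% |
| Random 12/15/18 | about 1.5% | 49% |
| Random 3/6/9 | about 4% | about 55% |
| Fixed 9 | 14.3% | 53% |
| Fixed 6 | 20.0% | 56% |
| Fixed 3 | 33.3% | 61% |

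Random large blocks remove most of the certainty but hardly change the average guess. Smaller blocks raise the average guess rate.

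**The case against.** The case for leaving this alone is substantial, and most of it stands.

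- **The fully informed observer is hypothetical.** The article describes no shared log. It says intervision is regular but not that allocations or their order are discussed. A therapist in an introduction session would also need to know how many other patients in that stratum had been randomised. A reader might infer that the five therapists know every past assignment. The text supports only that each knows the arms of the patients they treat.
- **Late-block certainty is easily overstated.** A reader might infer that the last two or three places in a block are often known. Even with full information, the 14th is certain in fewer than three blocks in ten and the 13th in about one in fifteen.
- **The usual route to selection bias is closed.** Screening, the diagnostic interview, consent and the lab baseline all come before the introduction session, so a guess made there cannot steer enrolment.
- **Expectancy can be examined.** Expected success is recorded at baseline and again after session 1.
- **The figures measure guessability, not bias.** Nothing in the article indicates which arm a therapist would favour or how far a Core Belief Interview contrast would move. The targets are also chosen jointly with the patient.
- **Fifteen is already a large block**, and better than 3, 6 or 9.
- **An article may leave concealment detail to the full protocol.** That is fair for who is told what. It does not cover the block size, which the article itself fixes and publishes.

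What survives is narrow: a constant, public block size creates certain assignments that need not exist, just before the one primary outcome that has no earlier baseline.

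**Conclusion.** The point holds as a minor design weakness that is cheap to improve. It is not evidence that allocation is compromised. The upper limit is 9.1% of assignments certain, at most about 14 of 150. That limit requires complete pooling within a stratum, knowledge of the block boundary and ten filled blocks. On a therapist's own caseload, prediction is about 36% against 33%, with nothing certain.

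Any bias would fall mainly on the content and baseline of the Core Belief Interview. Its size and direction cannot be derived from the article, so it is right to say that prediction could bias those contrasts, not that it does. The simulated rates also rest on patients being spread at random over therapists.

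**What to change.** For the remaining blocks, have the script draw each block size at random from large multiples of three, for example 12, 15 and 18, separately within each severity stratum. Do not disclose the sizes to therapists, and keep the running list of allocations by stratum from them, including in intervision. Withholding the list matters at least as much as varying the sizes, because the average guess rate moves only from 50% to 49%. The gain from varying sizes is the fall in certain assignments from 9.1% to about 1.5% for a fully informed observer.

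Do not use small blocks such as 3/6/9, which raise the guess rate to about 55%. Locking the interview before the assignment is released would not address prediction, and randomising after the interview is already the stated order.

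The cost is a small script change and one sentence in the protocol, with no extra patients or staff. Final arm totals may be slightly less even: one unfinished block can leave two arms in a stratum up to 18/3 = 6 apart, instead of 15/3 = 5.

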#### Primary Outcome: Therapy Processes

##### CBT Skills

CBT skill acquisition will be measured in two different ways. First, before and one week after the therapeutic procedure patients will complete the Ways of Responding (WOR; Barber & DeRubeis, 1992). During the WOR, CBT skills of the participants are tested by asking them to think about themselves in various situations and to tell what they would think and do in such situations. The WOR will reflect the level of CBT skills demonstrated by the patient. Patients will receive three scenarios before treatment and three different scenarios after treatment. Answers to each scenario will be coded into 25 different categories (more categories per answer possible) and given a rating of the overall quality of the response (i.e., the raters’ judgment on how well the response would be in improving mood or adjusting to the individual’s needs, range = 1 (very negatively) to 7 (very positively)). The total score will be composed of the number of responses on positive categories (responses considered consistent with CBT) minus the number of responses on negative categories (depressotypic statements). Interrater reliability showed to be high (ranging from α = .91 to α = .98) and discriminant and convergent validity have been supported (for example: the WOR showed no correlation with a measure of self-control, but was correlated to self-report measure of CBT skills) (Barber & DeRubeis, 2001; Strunk et al., 2014). Second, change in CBT skills during the procedures will be measured using the Behavioral Activation for Depression Scale – short form (BADS-SF) (BA skills) and Cognitive Change Sustained Change (CCSC) (CT skills). The BADS-SF consists of nine items, each rated on a 7-point Likert Scale and internal consistency (α = .81) and construct and predictive validity were supported (for example: the BADS-SF was positively related to measures of reward, negatively related to measures of avoidance and predicted time spent in high and low rewarding behavior; Manos et al., 2011). An example item from the BADS-SF is: ‘There were certain things I needed to do that I didn’t do’. The CCSC consists of 9 items rated on a 7-point Likert scale and internal consistency was supported (α = .93) and the scale showed convergent and discriminant validity by showing a relation with a self-report scale of CBT skills and no relation with a measure of attributional styles (Schmidt et al., 2019). An example item from the CCSC is: ‘I noticed myself thinking less negatively.’

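### Randomisation is stratified by depression severity but the stated models do not name the stratum; if severity is prognostic, standard errors are conservative, by little for change contrasts and by more for between-patient contrasts

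*Protocol article*

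**What the plan says.** Under Randomization and Procedure, allocation uses "block randomization (1:1:1, block size = 15"), and "Randomization will be pre-stratified on severity of depression", with strata "mild [Beck Depression Inventory-II (BDI-II) = 14-19] vs. moderate to severe" (20 or more). Randomisation follows the introduction session.

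Under Main Analyses, the three pairwise condition comparisons on primary and secondary outcomes use "multilevel analysis with maximum likelihood estimation (measurements [Level 1] nested within patients [Level 2] nested within therapists [Level 3"). The WOR is treated separately: "differences between conditions on the WOR will be tested using a repeated measures ANOVA". The only further fixed terms named are those for moderation: "adding learning capacity as a main factor and the interaction between learning capacity and condition to the multilevel regression model". Neither the severity stratum nor baseline BDI-II is named, and nothing says that severity is excluded. The time terms are not written out.

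Table 1 gives every primary and secondary outcome a measurement at baseline or at the introduction session, so before randomisation. For the WOR, "before and one week after the therapeutic procedure patients will complete the Ways of Responding".

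**The concern.** Blocking within strata balances severity across the three conditions. If severity is related to the outcome, the true sampling variance of a condition contrast falls. A model without the stratum leaves that variance in its error term, so its reported standard error does not show the gain. Intervals come out too wide, the actual type I error falls below 0.05 and power is lower than the design allows.

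The stake is precision, not validity. It matters somewhat because pairwise power is modest. With 50 × 0.8 = 40 completers per arm and an assumed d of 0.5 (the article says only that the effect is medium), a two-sided 0.05 comparison has power of about 0.61 by normal approximation.

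**Working it through.** **Inputs from the article.** Two strata; 1:1:1 allocation in blocks of 15; alpha 0.05 two-sided; 150 patients with 20% drop-out, so 120 completers; a pre-randomisation measurement of every outcome.

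**Assumed, because the article does not give them.** 30% of patients mild; a stratum gap of 1 within-stratum SD; within-patient correlation 0.5.

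**1. The plan's own sample size.** For a between-patient main effect in a repeated measures ANOVA, λ = N·f²·m / (1 + (m − 1)ρ). Take f = 0.25 (assumed for medium), three groups and ρ = 0.5.
- m = 2, N = 120: λ = 120 × 0.0625 × 2 / 1.5 = 10.0, power 0.805.
- m = 4, N = 102: λ = 102 × 0.0625 × 4 / 2.5 = 10.2, power 0.811.

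This reproduces the stated 102 to 120, and 120 / 0.80 = 150. The recruitment target therefore matches a between-patient main effect.

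**2. General relation.** If the stratum explains a share R² of the variance of the quantity tested, reported SE / true SE = 1/√(1 − R²), and actual alpha = 2·(1 − Φ(1.96/√(1 − R²))). Power below is for a pairwise contrast with d = 0.5 and 40 per arm.

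| R² (assumed) | SE too wide by | Actual alpha | Power without stratum | Power with stratum |
|---|---|---|---|---|
| 0 | 0% | 0.050 | 0.609 | 0.609 |
| 0.01 | 0.5% | 0.049 | 0.609 | 0.613 |
| 0.05 | 2.6% | 0.044 | 0.612 | 0.631 |
| 0.10 | 5.4% | 0.039 | 0.615 | 0.654 |
| 0.20 | 11.8% | 0.028 | 0.621 | 0.705 |

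For a test of change, R² is the stratum's share of the variance of change, not of the outcome's level.

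**3. Post-only contrast.** The stratum contributes 0.3 × 0.7 × 1² = 0.21 to a within-stratum variance of 1, so the ratio is √1.21 = 1.10. A simulation of stratified 1:1:1 allocation (120 completers, 4,000 replicates) gave a model SE of 0.2462 without the stratum and 0.2232 with it, a ratio of 1.10, and an actual alpha of 0.033 without it. The result follows the gap at the time analysed. With a post-treatment gap of 0.5 SD the model SEs were 0.2297 and 0.2237 (2.7% too wide). With 1.5 SD they were 0.2719 and 0.2231 (22%).

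**4. Change contrast (equal to condition by time with two occasions, the WOR case).** The within-stratum variance of change is 2 × (1 − 0.5) = 1.
- Stratum shifts level only: it cancels from change. Model SE 0.2232 with and without the stratum.
- Stratum also shifts change by 0.5 SD: 0.21 × 0.25 = 0.0525, ratio √1.0525 = 1.026. Simulated 0.2294 against 0.2234, 2.7% too wide.

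**5. Mixed model.** Six occasions, random patient intercept, no therapist level, stratum gap shrinking by 0.05 SD per occasion, 30 replicates.

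| Term | No stratum | Stratum | Stratum × time |
|---|---|---|---|
| SE, condition × time | 0.0381 | 0.0381 | 0.0380 |
| SE, condition | 0.2146 | 0.1943 | 0.1942 |

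The condition-by-time SE barely moves. The condition coefficient's SE is 0.2146 / 0.1943 = 1.10 times as large without the stratum. That coefficient is the between-patient difference at time zero. A main effect averaged over two occasions would lose slightly more: the within-stratum variance of the patient mean is (1 + 0.5)/2 = 0.75, so the ratio is √((0.75 + 0.21)/0.75) = 1.13.

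**The case against.** A reader might infer that the models exclude severity and that the standard error of every condition contrast is therefore too wide. The article supports neither step.

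On exclusion, Main Analyses is a condensed account. It also leaves out time terms and covariance structure, and a covariate list is commonly left to the full protocol or analysis plan. Not naming the stratum is not the same as ruling it out. That objection stands, and it limits the point to asking for one term to be stated.

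On every contrast, the stated aim is change. The models are longitudinal, each outcome has a pre-randomisation value, and patient is a level in the multilevel model. A stable severity difference then drops out of condition-by-time tests, as steps 4 and 5 show. That also stands.

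It does not dispose of the point, because the article does not commit to a condition-by-time test. The sample size of 150 matches a between-patient main effect, and the moderation term is learning capacity by condition with no time term named. Both leave open the reading under which the loss is larger.

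**Conclusion.** The point holds as a modest one. The design stratifies on severity and the stated models do not name the stratum. Any effect is conservative and arises only if severity predicts the quantity tested.

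Under the assumptions above, the standard error is 0 to about 3% too wide for change contrasts. It is about 10% too wide for a post-only contrast or the condition coefficient, and somewhat more for a main effect averaged over occasions. These sizes are illustrative: the article gives no correlation between the BDI-II split and any outcome or its change, no proportion of mild patients and no within-patient correlation. A certain loss, or one common to all contrasts, cannot be claimed from it.

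**What to change.** State in Main Analyses that the severity stratum enters as a fixed effect, with its interaction with time, in every primary and secondary multilevel model. In the WOR analysis, enter it as a between-patient factor with stratum by time. Write out the time terms and say which coefficient carries the condition comparison.

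Do not simply add each outcome's baseline value to these models, because the baseline would then be both response and covariate. If baseline adjustment is wanted, take the baseline out of the outcome vector first. The BADS-SF, CCSC and BDI-II have two scores before randomisation (baseline and introduction session), so say how both are handled. For the WOR this means an ANCOVA of the follow-up score on condition, baseline WOR and stratum. In the level-only simulation its model SE was 0.1941, against 0.2232 for the change analysis.

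The cost is a sentence or two and a few degrees of freedom: two with linear time (stratum, stratum × time), and up to six for the BDI-II with categorical time (1 + 5 over its six occasions in Table 1). No new data are needed.
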